### Interim analyses {21b}

This trial is not planned as a group-sequential or adaptive trial. Hence, we have no interim analyses.

### Methods for additional analyses (e.g., subgroup analyses) {20b}

Instead of subgroup analyses, explorative moderator analyses are planned. Possible moderators for DiGA use are sex, age, severity of depressive symptoms, treatment setting, education, media affinity, eHealth literacy, cognitive function, and current or former use of health apps or DiGA. Moderator analyses will be performed using the logistic regression model from the primary endpoint analysis with an additional inclusion of the treatment x moderator interaction.

All moderator analyses are exploratory. Further exploratory analyses are done to identify predictors of DiGA use. This analysis will be done only in the control group.

Feasibility of a multi-center trial will be explored by consideration of recruitment rates, observed difference in depressive symptoms (PHQ-9), and patient’s satisfaction with the intervention.

### Methods in analysis to handle protocol non-adherence and any statistical methods to handle missing data {20c}

Two differing data sets are defined for the analyses:

#### Full analysis set (FAS)

The FAS, based on the ITT strategy, is defined as all randomized patients according to their allocated intervention group, who fulfill the inclusion criteria and do not fulfill any exclusion criteria.

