## Interventions

### Explanation for the choice of comparators {6b}

The control intervention is treatment as usual. After DiGA prescription, patients receive a short information by their treating physician, and the manufacturer’s information film about the DiGA is shown. The further process of activating the DiGA and its use are the responsibility of the patient.

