### Intervention description {11a}

In addition to a short information by the treating physician after DiGA prescription and the manufacturer’s film, the intervention group receives the offer of regular individual support by a digital nurse who accompanies and supervises the process of request to the health insurance companies, the installation of the app/navigation to the website until the first use of the DiGA up to 8 weeks according to the needs of the patients. The consultations are offered in different ways depending on the patient's needs: by telephone, via video call or face to face. Support is actively offered to patients at least once a week. The digital nurses are trained particularly in the process of prescription and establishing contact with the DiGA manufacturer and the health insurance company. Furthermore, the digital nurses are trained in the installation and application of the DiGA. Within the counseling process, the digital nurses should respond attentively and sensitively to the needs of the participants. They will therefore be trained in motivational interviewing techniques like active listening and change talk. The digital nurses also monitor the emotional state of the participants in order to identify mental crises and suicidal tendencies, that might necessitate intensive care in inpatient settings as well as exclusion from the study.

A guideline is developed that defines the counseling process and the care options. Checklists will be used to ensure fidelity to the guideline. In order to develop best practice guidelines number of sessions, mode and duration of intervention, total support time, and discussed topics will be documented during each counseling session.

The trained digital nurse supports the individual participant in using the DiGA for up to 8 weeks or until the first use of the DiGA, whichever comes first (intervention phase). This means that at the time the participant is able to start the first session of the DiGA, the support of the digital nurse ends. However, the digital nurse will be available to patients until week 16 if they have any problems or questions regarding the DiGA application (follow-up phase).

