### Criteria for discontinuing or modifying allocated interventions {11b}

Participants are able to discontinue the study intervention at any time without giving reasons and without suffering any disadvantage, as stated to them prior to informed consent. The study intervention will be discontinued, if it becomes apparent that the system requirements for using the DiGA are not met. Furthermore, study intervention (seeking contact through the digital nurse) will be stopped, if it becomes apparent that the patient's mental or somatic health has deteriorated significantly, and the patient is currently unable to use the DiGA.

When a subject discontinues from the study intervention but not from the study, the remaining study assessments will be completed as indicated by the study protocol.

The data to be collected at the time of study intervention discontinuation will include the following:Point in timeThe reason(s) for discontinuing the intervention.If possible, the primary endpoint and depressive symptoms at the time of discontinuation.

Thereafter, the participant will be included in all future scheduled assessments, even though not participating in the intervention.

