#### Primary and secondary endpoints

For the primary endpoint, the main aim is to estimate the odds ratio (OR) of DiGA use with digital nurse support vs. unsupported prescriptions. The confirmatory analysis will be conducted in the full analysis set (FAS, see below) based on the intention-to-treat (ITT) principle. The analysis of the primary endpoint is carried out using a logistic regression model. In addition to the intervention group, the model also includes age, gender, and the recruiting center as well as possible other factors as covariates. One-sided *p*-value corresponding to the hypothesis given above, estimated OR and corresponding one-sided confidence interval will be reported. One-sided *p*-value will be calculated as half of the *p*-value from the fitted model output.

Analyses of all secondary outcomes are exploratory and will be done as complete case analyses, meaning that only cases with available data for the analysis are included. Analysis of the secondary efficacy outcomes will be undertaken following the same framework as the primary outcome model, particularly using the same covariates in the models. For each continuous outcome including the PHQ-9 and SUS, a linear regression model will be fitted. For the analysis of PHQ-9, the baseline value is included in the model as an additional covariate. The estimates for the group effect with accompanying 95% confidence intervals and two-sided *p*-values will be reported. Details of the models will be specified in the statistical analysis plan (SAP).

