#### Safety analysis dataset

The safety analysis set will include all randomized patients.

Missing values of the primary endpoint will be imputed. Details of the model, imputation of missing values and sensitivity analysis will be specified in the SAP.

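### The confirmatory set is labelled ITT but removes ineligible patients after randomisation with no time limit, and the device criterion could remove non-starters preferentially from the nurse arm

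*Protocol article*

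**What the plan says.** Under Primary and secondary endpoints, the protocol article states: "The confirmatory analysis will be conducted in the full analysis set (FAS, see below) based on the intention-to-treat (ITT) principle". The section Full analysis set (FAS) then defines that set as "all randomized patients according to their allocated intervention group, who fulfill the inclusion criteria and do not fulfill any exclusion criteria". The only set that keeps everyone is the one for safety: "The safety analysis set will include all randomized patients". The FAS definition gives no reference time for eligibility and no condition that both arms be examined equally.

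Four other sections bear on how ineligibility comes to light:

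- **Eligibility criteria {10}** makes access to a device on which the DiGA can be used an inclusion criterion.
- **Criteria for discontinuing {11b}** foresees a later device failure: "The study intervention will be discontinued, if it becomes apparent that the system requirements for using the DiGA are not met".
- **Intervention description {11a}** has the nurse supervise installation up to first use, and "Support is actively offered to patients at least once a week". The nurse also watches for mental crises "that might necessitate intensive care in inpatient settings as well as exclusion from the study".
- **Choice of comparators {6b}** says of the control arm: "The further process of activating the DiGA and its use are the responsibility of the patient".

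**The concern.** Removing ineligible patients after randomisation can be defended when the breach existed before randomisation, both arms are examined equally, and the decision is blind to arm. The FAS definition states none of these conditions, and the design works against equal examination.

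The device criterion is the weak point because it is tied directly to the primary endpoint, which is whether the first session was started within 8 weeks. A patient whose device cannot run the DiGA cannot start. In the nurse arm, a trained person works through installation with that patient and is likely to find the cause. A control patient with the same device may simply not start, and then counts in the FAS as a non-user. If the first patient is reclassified as having failed an inclusion criterion, one certain non-starter leaves the nurse arm while the matching control stays. The nurse-arm use rate rises without any effect of the nurse. The bias points towards the hypothesis under test and affects the trial's only confirmatory comparison.

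**Working it through.** **1. The plan's own figure.** Sample size {14} assumes 30% versus 50%, Fisher's exact test, one-sided 5% and 80% power. Full enumeration of the two binomials gives power 79.8% at 83 per group and 80.5% at 84, so 84 is reproduced. Allowing for dropout, 84 / (1 − 0.15) = 98.8, which is 99, so 100 per group is consistent. The sample size is not in dispute.

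**2. Inputs for the bias check.** From the documents: 100 per arm, 30% use under control, one-sided 5%, analysis by logistic regression. Assumed: no true effect (30% in both arms), k non-starters removed from the nurse arm and j from the control arm. The documents give neither k nor j.

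**3. Apparent rate and odds ratio.** With 30 expected starters per arm, the nurse-arm rate is 30 / (100 − k). The apparent odds ratio is [30 / (70 − k)] / [30 / (70 − j)] = (70 − j) / (70 − k). For k = 5 and j = 0 these are 30/95 = 31.6% and 70/65 = 1.08.

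**4. Rejection rate.** Starters in the nurse arm follow Bin(100 − k, 30 / (100 − k)) and in the control arm Bin(100 − j, 30 / (100 − j)). Every pair of counts is enumerated. The null is rejected when the log odds ratio divided by its Wald standard error, √(1/a + 1/b + 1/c + 1/d), exceeds 1.645. This is the unadjusted version of the planned logistic test; the planned covariates are not modelled.

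| k (nurse) | j (control) | Nurse-arm rate | Apparent OR | One-sided type I error |
|---|---|---|---|---|
| 0 | 0 | 30.0% | 1.00 | 5.0% |
| 1 | 0 | 30.3% | 1.01 | 5.5% |
| 2 | 0 | 30.6% | 1.03 | 6.0% |
| 5 | 0 | 31.6% | 1.08 | 7.6% |
| 10 | 0 | 33.3% | 1.17 | 12.1% |
| 5 | 3 | 31.6% | 1.03 | 6.1% |
| 10 | 5 | 33.3% | 1.08 | 9.1% |

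**5. Sensitivity to the test.** In a variant that removes exactly k non-starters from the nurse arm, a pooled score test gives 8.0% at k = 5 and 12.4% at k = 10 (5.1% at k = 0). Fisher's test, which is conservative, gives 5.8% and 9.5% (3.7% at k = 0). The direction is the same throughout.

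**The case against.** The strongest case against has four parts.

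**Most ineligibility is settled before randomisation.** Screening has two steps, final eligibility is judged at the baseline visit, and the allocation is released only after baseline measurement. Both arms are contacted at weeks 8 and 16, and data review is blinded. This stands as far as it goes: it narrows the differential route largely to device failure and makes a large k hard to support. Blinded review limits discretion over recorded breaches, but it does not equalise how often they are discovered.

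**Section {11b} points away from removal.** When system requirements prove unmet, it is the intervention that stops, and assessments continue. Nothing there says the patient leaves the FAS. That is correct. Removal follows only if the failure is read as a breach of the device criterion, which the FAS definition allows but does not state.

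**A reader might infer that a crisis or suicidality detected by the nurse also removes patients from the FAS.** The documents do not support this firmly. The criterion concerns current suicidality and is checked at enrolment or baseline, so a crisis arising weeks later is not clearly a breach of an entry criterion.

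**A reader might also infer that {11a} and {11b} contradict each other outright.** They can be read as two statuses: leaving the study, and stopping only the intervention. What remains is that the text does not say which applies when the nurse detects a crisis.

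Deferring sensitivity analyses to the SAP does not answer the point, because the protocol itself fixes the confirmatory set.

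**Conclusion.** The point holds in a bounded form. The mismatch between the ITT label and the FAS definition is explicit in the text. Preferential removal from the nurse arm is an inference, supported by the device criterion, the expected late discovery of device failure and the unequal contact between arms. It is not a stated procedure.

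The size depends on an unknown count. One or two one-sided removals move the type I error from 5.0% to 5.5% or 6.0%; five give 7.6% and ten give 12.1%. Removal from one arm only is the extreme case, and any detection in controls shrinks the excess. These figures assume no true effect, 30% use, 100 per arm, that every removed patient is a non-starter, and an unadjusted test. It would go too far to say that non-starters will be removed from one arm only, or that the error will reach double figures: the documents give no basis for a count that high after eligibility screening. The direction, in favour of the nurse arm, does not depend on the count as long as more non-starters are removed there.

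**What to change.** Define the FAS as all randomised patients, analysed as allocated, with no removal for eligibility. This is the population already named for safety. Missing primary outcomes are imputed as the protocol already plans. If an eligibility-restricted analysis is wanted, make it a sensitivity analysis that drops patients only on facts documented before randomisation and judged blind to arm.

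The cost is a wording change in the protocol and the SAP. A few truly ineligible patients stay in and dilute the effect slightly. The sample size of 84, raised to 100 per group, stays as it is.

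Separately, the sponsor should reconcile Intervention description {11a} with Criteria for discontinuing {11b}, so that it is clear which study status applies to a patient in whom the nurse detects a crisis.

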#### Safety analysis dataset

The safety analysis set will include all randomized patients.

Missing values of the primary endpoint will be imputed. Details of the model, imputation of missing values and sensitivity analysis will be specified in the SAP.

### Plans to give access to the full protocol, participant-level data, and statistical code {31c}

Full study protocol will be published in an international scientific journal. Study results will be published, regardless of whether the results are positive or negative, according to the Consolidated Standards of Reporting Trials (CONSORT). The SAP will be published as an appendix in the publication of results. Access to the participant-level dataset and statistical code will be given upon request after analyses have been finished.

## Oversight and monitoring

### Composition of the coordinating center and trial steering committee {5d}

The overall coordinating center is the Institute of General Practice and Family Medicine (AM RUB) of the Ruhr-University Bochum; the head of the department is the head of the DiGA4Aged consortium. A trial steering committee will be established to provide expert advice and oversight and ensure that the trial is conducted to the required standards. The steering committee includes the respective leading investigator for the setting of General Medicine, Geriatrics, Psychosomatics (PI of the RCT), and Psychiatry as well as Biometry. The steering committee is responsible for agreement of the final protocol, protocol changes, and reviewing progress throughout the study. Scientific assistants and digital nurses control the trial progress on a day-to-day basis.

### Composition of the data monitoring committee, its role and reporting structure {21a}

Since this study is being conducted with an approved DiGA, it is a low-risk study, so only reduced monitoring will be done. Each clinical site will perform internal quality management of study conduct, data collection, documentation, and completion. Quality control procedures will include:

Informed consent—Study staff will review both the documentation of the consenting process as well as a percentage of the completed consent documents. This review will evaluate compliance with good clinical practice, accuracy, and completeness. Feedback will be provided to the study team to ensure proper consenting procedures are followed. A data monitoring committee is not needed, see item 22 below.

### Adverse event reporting and harms {22}

This trial investigates the possible increase in DiGA use due to a digital nurse. The DiGA is listed in the DiGA register and can be prescribed without any safety concerns. The intervention itself therefore is relatively low risk. This is a trial to investigate feasibility and proof of concept. We do not expect significant adverse effects arising from the trial itself. We have therefore decided not to have a separate data monitoring and safety board. Oversight of the trial will be managed by the trial steering committee.

### Frequency and plans for auditing trial conduct {23}

At the beginning of the study, the whole consortium including the trial steering committee (see {5d} above) will meet every 2 weeks in order to properly initiate the trial and review trial conduct. During the recruitment phase, the meetings then take place monthly. The project management and digital nurses meet every 2 weeks in order to discuss trial progress and problems. The recruitment process is reported every month. Recruitment figures are continuously compared with the target; if necessary, measures to increase patient numbers can be discussed in the management team on an ongoing basis. Plausibility checks of the data are already carried out in the course of the study and corresponding queries are sent to the centers to ensure high data quality. Further aspects of internal data monitoring and quality control have been described in section {21a}. External audits are not planned.

### Plans for communicating important protocol amendments to relevant parties (e.g., trial participants, ethical committees) {25}

The project management communicates the necessary amendments to the study protocol with the responsible ethics committees and, if approved, updates the information in the clinical trials registry. The amendments are communicated to the leading investigators of the four participating study centers including the PI. The site investigators are responsible for communicating the amendments to the study personnel involved and, where relevant, also to participants of the respective study site.

### Dissemination plans {31a}

The results will be published in a final report in accordance with the sponsor’s guidelines. In addition, scientific results will be disseminated through publications in peer-reviewed scientific journals that comply with the International Committee of Medical Journal Editors’ guidelines for authorship and through presentations at national and international scientific conferences.

## Discussion

The use of digital health interventions in Germany is growing but has room for improvement. Older adults use health apps and DiGA less frequently than younger adults, probably due to reduced health literacy and digital skills, and lack of support. Previous studies suggest that mobile apps can be helpful in reducing care and symptom severity in somatic and mental disorders [3]. However, it has also been shown that adherence can be significantly improved through support [34]. With the rise of digitalization in the healthcare system, the implementation of a trained digital nurse is an exciting path that ideally also saves time for the treating physicians.

The results of this RCT study will give insights into the feasibility of recruiting adults with depression aged 60 years and older for the use of a depression DiGA. As a proof of concept study, this trial will also give evidence of the efficacy of support by a digital nurse in using the prescribed DiGA. Factors that might moderate the effect, such as sociodemographic factors, living situation and assistance, media affinity, or digital health literacy will be explored.

Qualitative and quantitative evaluations of the trial implementation will result in best practice guidelines on how to support and improve DiGA prescription and successful use by older adults with mild to moderate depression. Barriers and facilitators of digital nurse support in older adults with mental illness will be revealed and compared to existing literature [34]. Moreover, the results of this study will be used to elaborate an overarching concept for successful digital nurse support for older adults receiving a DiGA prescription, regardless of the underlying disease.

This study aims to investigate whether the use of digital nurses to support patients in installing and starting DiGA treatment is successful. If so, this would strongly support the implementation of digital nursing in clinical routine. These could be medical assistants or digital-savvy students who receive a short training course. This could optimize medical resource consumption and at the same time strengthen the therapeutic benefits of DiGA. This concept will include a discussion on the implementation against the background of the current health care in Germany and underlying statutory regulations, possibilities of financing a digital nursing concept in vulnerable populations, and the required qualification of non-medical staff in order to deliver digital support.

## Trial status

Recruiting started in July 2024. The current protocol is version 4.0 of 15–07–2024. Patient recruitment is estimated to be completed around July 2025.

## Data Availability

Data collected for this study will be analyzed and stored at the AMIB for 10 years from the completion of the study. When the study is completed, access to study data will be provided upon request to the principal investigators.

## Abbreviations

AMIB: Department of Medical Informatics, Biometry and Epidemiology
CONSORT: Consolidated Standards of Reporting Trials
CRF: Case Report Form
DVG: Digitales Versorgungsgesetz (Digital Health Care Act)
DiGA: Digitale Gesundheitsanwendung (digital health application)
eCRF: Electronic Case Report Forms
FAS: Full analysis set
GCP: Good Clinical Practice
ICH: International Council on Harmonisation
ITT: Intention-to-treat
MOP: Manual of Procedures
PHQ-9: Patient Health Questionnaire-9
PI: Principal Investigator
UEQ: User Experience Questionnaire
SAP: Statistical analysis plan
SUS: System Usability Scale
SOP: Standard Operating Procedure
